## Abstract

**Introduction:** Mobility impairments are among the main causes of falls in older adults and patients with neurological diseases, leading to functional dependence and substantial health care costs. Feedback-based interventions applied in controlled, laboratory environments have shown promising results for mobility rehabilitation, enhancing the benefits of standard therapy. However, the effectiveness of sensor-based feedback to improve gait in actual outpatient physical therapy settings is unknown. The proposed trial examines the effectiveness of a physical therapist-assisted, visual feedback system using wearable inertial sensors, Mobility Rehab, for mobility training in older adults with gait disturbances in an outpatient clinic.

**Methods:** The study is a single site, pragmatic clinical trial in older adults with gait disturbances. Two hundred patients undergoing their outpatient rehabilitation program are assigned, by an independent assistant, for screening by one of four therapists, and assigned to either a standard physical therapy or therapist-assisted feedback therapy. Both groups train twice a week for 6 weeks. Four physical therapists were randomized and stratified by years of experience to deliver standard therapy or therapist-assisted feedback rehabilitation. Each session is 45 min long. Gait is trained for 30 min. The additional 15 min include exercises for endurance, strength, and static and dynamic balance in functional tasks. Mobility Rehab uses unobtrusive, inertial sensors on the feet and belt with real-time algorithms to provide real-time feedback on gait metrics (i.e., gait speed, double support time, foot clearance, angle at foot strike, and arm swing), which are displayed on a hand-held monitor. Blinded assessments are carried out before and after the intervention. The primary outcome measure is subjects' perception of balance as measured by the Activities-specific Balance Confidence scale. Gait speed, as measured with wearable inertial sensors during walking, is the secondary outcome measure.

**Discussion:** We hypothesize that therapist-assisted feedback rehabilitation will be more effective than standard rehabilitation for gait. Feedback of motor performance plays a crucial role in rehabilitation and objective characterization of gait impairments by Mobility Rehab has the potential to improve the accuracy of patient-specific gait feedback.

**Clinical Trial Registration:**www.ClinicalTrials.gov, identifier: NCT03869879.

## Introduction

Gait training in physical therapy has been shown to improve gait (1–4). However, benefits are not optimal yet. Often, it is difficult for physical therapists (PTs) to observe subtle abnormalities in gait patterns and difficult to provide quick accurate feedback about gait impairments to their patients. For example, abnormalities of duration of double support time, foot clearance or angle of the foot at heel strike may be difficult to observe, yet they are important characteristics to improve to avoid falls (5, 6). PTs and patients would benefit from using a reliable system to efficiently and accurately quantify gait impairments, provide cues on how to modify abnormal gait patterns and quantify each patient's response to therapy.

Gait and balance impairments are among the most common causes of falls in older adults and neurologic patients (7, 8). Gait impairments often manifest as slow gait with increased double support time, reduced foot clearance, reduced angle at foot strike, decreased arm swing, and increased variability of these measures (5, 9, 10). These impairments are usually multifactorial (11) and require a comprehensive assessment to identify persons at increased risk of falling and inform interventions (5). Many falls could be preventable through improved screening for gait disorders and training of those at increased risk (12, 13).

Feedback-based systems have been successfully used in laboratories for the treatment of gait abnormalities in clinical populations (14–17), exceeding the efficacy of standard physical therapy (18). However, most gait feedback systems are limited to treadmill walking, which is different from over-ground walking (19, 20), and they are limited to lower limb-related metrics. Mobility Rehab (APDM Wearable Technologies – an ERT company, Portland, Oregon, USA) was developed for both overground and treadmill walking and provides feedback about trunk and upper limb movements, as well as lower limb movements. The system uses wireless, wearable, inertial sensors (Opals) on the wrists, feet and trunk to improve the accuracy and effectiveness of PTs' feedback to their patients by providing objective measures of gait in real-time. Mobility Rehab provides therapists stride-by-stride, relative measures of gait quality, as well as summary statistics, on a tablet as their patient walks over-ground in natural conditions so they can provide quick, accurate verbal instructions to their patients.

There is a need to establish the effectiveness of therapist-assisted feedback in an actual outpatient therapy setting. The effect of feedback-assisted rehabilitation of gait and balance has mostly been investigated in laboratory settings (18, 21). It is unknown if successful application of feedback-based interventions is effective in an actual outpatient physical therapy clinic that provides gait and balance training to older adults with mobility disturbances. Here, we will conduct a pragmatic clinical trial in a large outpatient clinic to examine the effectiveness of the Mobility Rehab system for mobility training in older adults with gait disturbances. We hypothesize that therapist-assisted feedback rehabilitation will be more effective than standard rehabilitation for gait.

## Methods and Analysis

### Trial Design

The study is a single-site, pragmatic, controlled clinical trial in older people with gait disturbances. The trial compares standard-of-care gait training by PTs with therapist-assisted feedback therapy using Mobility Rehab in the same clinic. Participants scheduled at the physical therapy clinic for gait training are assigned to one of the four PTs, and that will determine, if eligible, their group assignment for the duration of their outpatient therapy. Assessments occur at baseline (pre) before intervention starts and immediately after the last session of intervention (post). The trial design is illustrated in Figure 1. This protocol paper follows the SPIRIT (Standard Protocol Items: Recommendations for Interventional Trials) 2013 statement and guidelines (22). SPIRIT template for the schedule of enrollment, interventions, and assessments is presented in Figure 2.

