### Recruitment and Screening

Outpatients coming for gait training at the Northwest Rehabilitation Associates clinic are invited to participate in this trial. Those who agree to learn more about the study are seen by a PT aide who explains the study further, completes a screening interview (for exclusion and inclusion), supervised by an experienced PT (MS), and obtains consent. There are no gender, ethnic, or racial minority exclusions for this study. Inclusion criteria include: 60–89 years old and gait disturbances requiring physical therapy. Any disease may be included and efforts are made to maintain an equal number of women and men in the sample. Participants are included in the study if they are able to follow instructions (up to the PT's judgement). This trial will stop enrolling participants when 200 individuals will have completed baseline and follow-up assessment.

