### Interventions

The two rehabilitation interventions for gait disturbances are: (1) standard-of-care physical therapy and (2) therapist-assisted feedback physical therapy. Both groups train twice a week for 6 weeks. Sessions are 45 min long and gait (with or without Mobility Rehab) is trained for 30 min in each session. The additional 15 min include exercises for endurance, strength, and static and dynamic balance in functional tasks. The difference between the two groups is the use of the Mobility Rehab system in the therapist-assisted feedback group. PTs design their own treatment plan for each patient. They are allowed to select modality, overground walking and/or treadmill, and tasks (dual task, head turns, etc.) as appropriate for each patient. During a regular session, patients work on gait with the following tasks for 30 min: weights on ankles, dual tasks, upper extremity support, partial body weight support, speed challenges, direction changes, obstacles, and head turning. The PTs using Mobility Rehab system underwent specific training on how to effectively use the system (e.g., sensors placement, software navigation, selection and interpretation of metrics, etc.) before the start of the trial.

The Mobility Rehab system uses unobtrusive, wearable, inertial sensors with real-time algorithms to provide real-time feedback on five gait metrics: step duration, stride length, arm range of motion, trunk coronal range of motion, and elevation at midswing (Figure 3). Therapists are allowed to select any gait metric and to focus on one or several gait metrics. The visual feedback is provided to a hand-held monitor/tablet (Figure 3) and displayed relative to age-specific normative values, which were previously collected from 120 healthy subjects between the ages of 60 and 89 years during a 2-min overground walk at a comfortable pace. Therapists also can select a minimum and maximum goal for a metric, based on each patient's abilities.

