### Sample Size and Power Analysis

#### ABC Scale

We anticipate most of our subjects will score in the 50–80 range on the ABC scale at baseline, although we will not exclude those with scores lower than 50. We extracted means and standard deviations (SDs) from published studies involving both community dwelling and home-care facility based older adults (23). Based on these studies, we assume our subjects will have an average score of 60 at baseline with a SD in the 11–20 range. Furthermore, a 12-point change in the scale has been reported to be clinically relevant (27). We anticipate that both the standard therapy and therapist-assisted feedback treatment groups will improve, but the feedback group will score at least 12 points higher on ABC scale at post-assessment. Thus, we anticipate group effect sizes between 0.6 and 1.2 SD for the current study. Type 1 error for the sole primary outcome was set to 0.05. Because we propose to randomize PTs rather than patients, there is clustering inherent in the study design (i.e., cluster-randomization). We account for clustering by computing power based on the effective sample size rather than the actual sample size (28). The effective sample size (ESS = m ^*^ (number of therapists)/DEFF) is based on the design effect (DEFF = 1 + (m – 1) ^*^ ICC), where ICC = intra-cluster (therapist) correlation and m = 50 is the anticipated # patients/therapist. We examined power to detect anticipated changes for a range of ICC between 0.002 and 0.010 [are based on values reported by Killip et al. (28)]. With 200 subjects equally allocated to each of the four therapists (two of which are randomized to therapist-assisted feedback group), the trial is adequately powered (84.3–96.1%) to detect effect sizes between 0.9 and 1.2 SD when ICC = 0,002; effect size of 1.1 SD is detectable with 82.6–91.1% power when ICC is higher (0.10).

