### Statistical Analysis

The analysis will adopt the intent-to-treat strategy. We will estimate and evaluate the difference in the post-assessment ABC between the two treatment groups, adjusting for participants' baseline characteristics (i.e., age, gender, and pathology). Since the outcome of interest is measured at the individual patient level, but PTs are the unit of randomization (i.e., PTs are assigned to either provide feedback in addition to usual care or not), we will fit a linear mixed effects model with post-assessment ABC as the dependent variable; fixed independent effects will be treatment group (therapist-assisted feedback therapy vs. standard therapy) and a random effect term to account for PT variability. The same model will be used to investigate changes on gait speed, our secondary outcome measure. Additionally, we will carry out a sensitivity analysis for those that complete at least 9 (out of 12) sessions to identify whether or not a certain number of sessions influences the observed effects, if any.

An exploratory analysis is proposed including estimating post-intervention differences in other gait metrics collected by the blinded assessor. These secondary gait outcomes will be fit with models similar to the primary outcome measure.

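### Tying the primary-outcome visit to the last session leaves early stoppers without a bookable visit and lets elapsed time vary; book it at the planned 6 weeks for everyone assigned

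*Protocol article*

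**What the plan says.** Trial Design in the protocol article places the two assessments as follows: "Assessments occur at baseline (pre) before intervention starts and immediately after the last session of intervention (post"). The text gives no day or window counted from baseline.

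Interventions gives one schedule for both arms: "Both groups train twice a week for 6 weeks". That makes 12 sessions. The same section leaves content to the therapist: "PTs design their own treatment plan for each patient".

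Statistical Analysis states that "The analysis will adopt the intent-to-treat strategy" and names the model: "we will fit a linear mixed effects model with post-assessment ABC as the dependent variable". The adjustment variables listed are age, gender and pathology, with a random effect for therapist; time since baseline is not among them. The section also anticipates incomplete attendance: "we will carry out a sensitivity analysis for those that complete at least 9 (out of 12) sessions".

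Recruitment and Screening sets the end of enrolment by completed pairs of assessments: "This trial will stop enrolling participants when 200 individuals will have completed baseline and follow-up assessment".

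**The concern.** The last session is an event after assignment. Patients and treating therapists influence when it happens, and neither is blinded: the therapists deliver the intervention, and patients are asked not to reveal their group to the assessors. With two therapists per arm, one therapist's habits in rescheduling or discharge affect about half an arm.

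Two things are at stake. The first is timing: patients who leave the planned course are measured earlier or later than week 6, and nothing in the rule keeps this equal between arms. The second is completeness: a patient who stops coming has no session that anyone knows at the time to be the last, so a visit immediately after it cannot be arranged. If such patients go unmeasured while enrolment continues until 200 pairs exist, the data describe mainly those who finished. An intent-to-treat comparison needs the outcome on everyone assigned.

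**Working it through.** **The plan's own figure.** Sample Size and Power Analysis gives 84.3–96.1% power for 0.9 to 1.2 SD at ICC = 0.002, with 4 therapists and 50 patients each. "Type 1 error for the sole primary outcome was set to 0.05"; the sidedness is not stated, and two-sided is used here.

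- DEFF = 1 + (50 − 1) × 0.002 = 1.098
- ESS = 200 / 1.098 = 182.1, or about 91.1 per arm
- Noncentrality = d × √(91.1 / 2), which is about 6.07 for d = 0.9 and 8.10 for d = 1.2
- Noncentral t with 4 − 2 = 2 degrees of freedom: power 84.3% and 96.1%

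The stated range reproduces. Assessment time is not an input, so neither the concern nor the fix changes the sample size or the power.

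**Elapsed time under the last-session rule.** With sessions held on schedule, weeks to last session = sessions / 2:

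| Last session | Weeks from start |
|---|---|
| 12 (planned) | 12 / 2 = 6 |
| 9 (cut-off in the sensitivity analysis) | 9 / 2 = 4.5 |
| 6 | 6 / 2 = 3 |
| 4 | 4 / 2 = 2 |

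Missed and rescheduled sessions push the last one past week 6. Taken literally, the rule therefore gives week 6 only to patients who keep to the schedule.

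**What a difference between arms would require.** The documents give no attendance by arm. The shift in mean assessment time is (excess proportion of stoppers in one arm) × (weeks early):

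- Stopping at session 9 is 1.5 weeks early. A 10-percentage-point excess gives 0.10 × 1.5 = 0.15 week. A 1-week shift needs an excess of 1 / 1.5 = 67 points.
- Stopping at session 4 is 4 weeks early. A 1-week shift needs an excess of 1 / 4 = 25 points.

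A large shift in mean timing thus needs a large attendance gap.

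**Who ends up in the analysis.** Follow one early stopper through the text:

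1. Trial Design ties the post visit to the last session.
2. That session is identified only when the patient fails to return, so the visit cannot be booked ahead.
3. The model has one outcome per patient, the post-assessment score, so a patient without it supplies no observed outcome.
4. The enrolment rule does not count this patient towards 200, and another is enrolled.

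If a proportion p of those assigned lack the post visit, reaching 200 pairs takes 200 / (1 − p) patients, of whom 200p / (1 − p) have no outcome. The article gives no value for p. The count of 200 is met whatever p is, so the target itself does not reveal the loss. The analysis of those with at least 9 sessions does not help, because it restricts further towards completers.

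**The case against.** The strongest reply is that the planned course is identical in both arms, so the last session of the intervention is nominally week 6 for everyone. That stands: variation arises only through departures from the schedule, and the article does not say that a patient who stops after session 4 is to be measured at week 2. It is silent on early stoppers.

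End-of-treatment assessment is also a legitimate choice in a pragmatic trial, and a visit window may be in the full protocol or in the schedule figure (Figure 2), neither of which is shown. This limits the point, but the text does name a trigger. Any window elsewhere would have to be reconciled with it.

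A reader might infer that the anchor also causes patients to receive different amounts of therapy. It does not: that comes from adherence and would persist at a fixed date. If feedback changes attendance, the resulting difference in outcome is part of the intent-to-treat effect.

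A reader might also convert weeks into ABC points by assuming a usual-care gain spread evenly over 6 weeks. The documents give no such gain. A slope during therapy also does not apply to a patient who has stopped, for whom only change without therapy matters, and no figure is given for that. Such a conversion should not be used.

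Finally, the loss of early stoppers is a risk rather than a reported fact, and the enrolment rule contributes to it independently of the anchor.

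**Conclusion.** The point holds in a limited form. For patients who leave the planned course, the last-session trigger makes elapsed time variable and gives early stoppers no visit that can be booked. With incomplete attendance expected and enrolment counted in completed pairs, following the text risks unequal timing and an analysed group of mainly completers, against the stated intent-to-treat strategy.

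A reader might go further and conclude that the arms will be measured at different times and the contrast is biased. The documents do not support that: they show no difference between arms, and neither its size nor its effect on ABC can be computed from them. The conclusion assumes that some patients depart from the schedule, as the article anticipates, and that no unseen window or early-stopper rule already deals with them. The stated power is unaffected. This is a cheap improvement, not an error in a figure.

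**What to change.** In Trial Design, schedule the post-assessment at the planned 6 weeks from baseline, with a stated window, for every assigned patient in both arms whatever the number of sessions attended. Book it at the baseline visit, keep it for patients who stop therapy early, and record its date and the sessions completed by then. Make the schedule figure agree. Entering elapsed time as a covariate would not be a substitute: it is determined after assignment and does nothing for patients who were never measured.

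The cost is protocol wording and scheduling, with the same assessors and the same single post visit. The therapy course is untouched. Some patients will be measured shortly before finishing make-up sessions, and early stoppers will make one separate trip.

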**Figure 1 F1:**
[figure not shown]
Flowchart of the study.

**Figure 2 F2:**
[figure not shown]
SPIRIT template for the schedule of enrollment, interventions, and assessments.

### Study Setting

The intervention sessions and blinded assessments are performed at Northwest Rehabilitation Associates, an outpatient rehabilitation center in Salem (Oregon, USA). The clinical trial outcomes will be analyzed and summarized by blinded investigators and statisticians from Oregon Health & Science University (OHSU, Portland, Oregon, USA).

### Recruitment and Screening

Outpatients coming for gait training at the Northwest Rehabilitation Associates clinic are invited to participate in this trial. Those who agree to learn more about the study are seen by a PT aide who explains the study further, completes a screening interview (for exclusion and inclusion), supervised by an experienced PT (MS), and obtains consent. There are no gender, ethnic, or racial minority exclusions for this study. Inclusion criteria include: 60–89 years old and gait disturbances requiring physical therapy. Any disease may be included and efforts are made to maintain an equal number of women and men in the sample. Participants are included in the study if they are able to follow instructions (up to the PT's judgement). This trial will stop enrolling participants when 200 individuals will have completed baseline and follow-up assessment.

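### As described, the primary model uses only patients with a post-assessment ABC score although the analysis is called intent-to-treat, and 200 means completers in one place and assigned patients in others

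*Protocol article*

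**What the plan says.** Under Recruitment and Screening, the protocol article fixes the end of enrolment by completed assessments: "This trial will stop enrolling participants when 200 individuals will have completed baseline and follow-up assessment".

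Elsewhere 200 has another meaning. The Abstract says "Two hundred patients undergoing their outpatient rehabilitation program are assigned". Assignment and Blinding has two physical therapists (PTs) treating 100 participants with standard therapy and two treating the other 100 with feedback. Sample Size and Power Analysis allocates 200 subjects equally to four therapists, 50 each.

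Under Statistical Analysis the principle is stated as "The analysis will adopt the intent-to-treat strategy", and for the primary outcome "we will fit a linear mixed effects model with post-assessment ABC as the dependent variable". Treatment group is a fixed effect, PT is a random effect, and the adjustment covariates named are age, gender and pathology. Baseline ABC is measured, but it is neither an outcome nor a named covariate. The one sensitivity analysis concerns attendance: "we will carry out a sensitivity analysis for those that complete at least 9 (out of 12) sessions". Trial Design places the post-assessment directly after the last intervention session.

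**The concern.** Intent-to-treat means that every assigned patient is accounted for in the arm of assignment. A model with a single post score per patient cannot do this for anyone who lacks that score. The random PT effect does not help: it handles clustering, not missing outcomes. A pre/post model or an imputation could draw on the baseline ABC of such a patient; the stated model cannot.

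The post visit is tied to the end of a 6-week, 12-session course, so patients who stop coming may be the ones not assessed. Each arm has only two PTs, so one PT's retention pattern can become a difference between arms. If loss differs by arm and lost patients differ in balance confidence, the comparison of post scores is shifted. Because recruiting continues until 200 patients have both assessments, the analysed number will be 200 whatever the loss, so a reader needs the number assigned and the losses to judge it.

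**Working it through.** **1. The plan's own power figure, to see which 200 it uses.** Inputs from Sample Size and Power Analysis: 4 therapists, m = 50, ICC = 0.002, type 1 error 0.05 (two-sided assumed, as the article does not say).

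- Design effect = 1 + 49 × 0.002 = 1.098.
- Effective sample size = 200 / 1.098 = 182.1.
- Noncentrality = d × √(182.1 / 4) = 6.07 at d = 0.9 and 8.10 at d = 1.2.
- Noncentral t with 4 − 2 = 2 degrees of freedom: 84.3% and 96.1%, as printed.

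The calculation therefore needs 200 patients with outcome data, which agrees with the recruiting rule. If 200 were the number assigned and 20% were lost (assumed), 160 would remain and power at 0.9 SD would be about 78%. The completer target protects power.

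**2. Number assigned.** The article gives no dropout rate, so a range is assumed. Assigned = 200 / (1 − loss), rounded up.

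| Assumed loss | Assigned | Without a post score |
|---|---|---|
| 5% | 211 | 11 |
| 10% | 223 | 23 |
| 20% | 250 | 50 |
| 30% | 286 | 86 |

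With any loss, 200 cannot be both the number assigned and the number with both assessments.

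**3. Who enters the model.** One outcome, the post ABC, is modelled per patient. A patient without it has no term in the likelihood, whatever else is known. A patient who attended few sessions but was assessed does have a term and stays in.

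**4. Possible bias.** In one arm, let p be the fraction lost and g the mean post ABC of assessed patients minus that of lost patients (the part not explained by age, gender and pathology). The full-arm mean is (assessed mean) − p × g, so the assessed mean is too high by p × g. The arm difference is shifted by

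bias = p(feedback) × g(feedback) − p(standard) × g(standard).

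All values of p and g below are assumptions:

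- Loss 20% feedback, 5% standard, g = 10: 0.20 × 10 − 0.05 × 10 = +1.5 points.
- Same losses, g = 15: 0.20 × 15 − 0.05 × 15 = +2.25 points.
- Loss 10% feedback, 20% to 30% standard, g = 12: −1.2 to −2.4 points.
- Loss 20% in both, g = 18 feedback and 6 standard: 3.6 − 1.2 = +2.4 points.
- Equal loss and equal g: 0.

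Against the 12-point target, 1.5 and 2.25 points are 12.5% and 19%. The direction can go either way.

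**The case against.** A reader might infer more: that dropouts are replaced, that the intent-to-treat label is false, and that the trial is in fact a completer analysis. The documents do not support that.

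- The sentence on ending enrolment is a recruiting rule and does not define an analysis set. Recruiting to a target of assessed patients is an accepted way to cover attrition, and step 1 shows that it fits the power calculation. Nothing says that patients are replaced or excluded.
- Completer would be the wrong word for treatment. An analysis restricted to at least 9 of 12 sessions makes sense only if patients with fewer sessions are in the main analysis.
- The article is silent on missing outcomes, which articles commonly leave to a full protocol or SAP. Neither is shown, so this silence is not a finding.
- The bias figures rest wholly on assumed losses and gaps. Nothing in the article points to unequal loss, and both arms follow the same schedule in the same clinic.
- The Abstract is condensed and speaks of assignment for screening, so its count is partly a matter of wording.

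All of this stands. It leaves two things that the article does state: a post-score model that does not use baseline ABC, and a count of 200 with two meanings.

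A further objection is technical and also stands in part. With one post measurement, a complete-case model with baseline ABC as a covariate rests on nearly the same assumption as a joint or imputation model. Most of the gain therefore comes from using baseline ABC. The fuller methods add that baseline-only patients belong to the analysis set and that the assumption is stated openly.

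**Conclusion.** The point holds in limited form. As described, the primary analysis uses only patients with a post score and does not use baseline ABC, while being called intent-to-treat. The number assigned will exceed the 200 given in the Abstract, the assignment section and the sample size section if any patient is lost.

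The consequence is possible bias, of unknown size and direction, when loss is related to baseline balance confidence and differs by arm. The illustration of 1.5 to 2.3 points depends on an assumed 20% versus 5% loss and a gap of 10 to 15 points; with equal loss and gap it is zero. There is no loss of power from the recruiting rule. It does not follow that the trial breaches intent-to-treat, since an unseen SAP may deal with missing scores. The change is worth making because it uses data already collected and improves on the model as published.

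**What to change.** 1. Define the intent-to-treat set as all patients assigned to a PT who have a baseline assessment, analysed in the arm of that PT.
2. Bring baseline ABC into the primary analysis in one of two ways:
   - model pre and post ABC jointly, with PT and patient random effects and arm-specific baseline means, and estimate the baseline-adjusted post difference; or
   - multiply impute post ABC by arm with baseline ABC in the imputation model, then fit the planned mixed model with baseline ABC added as a covariate.

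   The baseline means should not be constrained equal across arms, because patients reach an arm through a PT's open schedule and are not individually randomised.
3. State the missing-at-random assumption and what it is conditional on.
4. Report losses by arm and by PT.
5. Keep the recruiting target, but say throughout that 200 is the number completing both assessments and not the number assigned.

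The cost is a little more programming and an assumption that must be defended in print; no more patients are needed. Bias from dropout that baseline does not explain would remain.
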